### Mindfulness-Based Stress Reduction

MBSR is an 8-week experiential program including 2.5-hour weekly class sessions and a 1-day silent retreat. MBSR engages participants in simple evidence-based mindfulness practices, including meditation, mindful walking and movement, cognitive reframing, and communication strategies. Pioneered in 1979 by [name] at the University of Massachusetts Medical Center, MBSR includes didactic and experiential training that teaches participants to cultivate self-awareness by redirecting attention away from past or future concerns and focusing instead on the present moment. With regular practice, participants learn to change habitual stress reactivity patterns and instead more flexibly respond to stress with adaptive coping. As a result, participants learn to avoid internalizing stress in reactive patterns of negative emotion [35] and, thus, reduce distress and prevent negative health and mental health outcomes.

WellNurse partnered with the University of California San Diego School of Medicine Center on Mindfulness and Brown University Mindfulness Center to provide remote, 8-week MBSR courses via Zoom and intensive week-long, in-person MBSR courses. MBSR was offered as an elective course to count toward the students’ elective requirements for Nursing. Additionally, faculty and staff were provided work time to participate in the program. Selected WellNurse project personnel including faculty, staff, and graduate students completed a multiyear teacher training certification process through the University of California San Diego and Brown University Mindfulness Center to develop a group of certified MBSR teachers to support long-term project sustainability.

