### MBSR Analysis

Quantitative evaluation of MBSR outcomes will be conducted by comparing MBSR participants with matched control participants at selected intervals with regard to key study variables (eg, stress, burnout, and mindfulness skills). Participants enrolled in MBSR are assessed immediately before their first MBSR session and immediately after completing the final MBSR session. Matched controls are identified for each MBSR participant by randomly selecting nonenrolled individuals from the WellNurse participant pool on the basis of identical gender identity, birth year, and role (faculty, staff, and student). Controls are assessed at the same intervals as MBSR participants.

Statistical analysis will test whether MBSR participants differ significantly from controls with regard to postintervention levels of each outcome variable, controlling for preintervention levels. ANOVA models will be used to conduct initial comparisons. With time, larger samples, and thus more statistical power and more complex models (eg, multilevel modeling), can be tested to evaluate the potential impact of instructor, delivery modality (in-person vs remote), duration (1 week vs 8 weeks), and dose (number of sessions attended), as well as individual participant characteristics (eg, gender identity and role). Ongoing assessments for all WellNurse participants will allow for longer term follow-up of MBSR and control participants with regard to distal outcomes of interest (eg, academic retention). We expect significant differences between MBSR and control participants; immediate postintervention effects may be strongest, with somewhat weaker longitudinal effects observed over time. Analyses will also be able to test whether those participants who engage in ongoing mindfulness practice after formal MBSR training may experience improved outcomes as compared with those individuals who discontinue regular practice.

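### With only remote 8-week and in-person 1-week MBSR courses described, the exploratory models cannot separate delivery modality from duration, and larger samples alone will not change that

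*Protocol article*

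**What the plan says.** Two places in the protocol article have to be read together.

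- **Delivery (Methods, interventions, Mindfulness-Based Stress Reduction).** The project worked with two university mindfulness centers "to provide remote, 8-week MBSR courses via Zoom and intensive week-long, in-person MBSR courses". Each modality is named with one duration. No remote 1-week course and no in-person 8-week course is described or planned anywhere in the article.
- **Analysis (Results, MBSR Analysis).** The planned comparison sets MBSR participants against matched controls on post-intervention scores, adjusting for pre-intervention scores, with ANOVA models at first. The section then looks ahead: "With time, larger samples, and thus more statistical power and more complex models (eg, multilevel modeling), can be tested", in order to "evaluate the potential impact of instructor, delivery modality (in-person vs remote), duration (1 week vs 8 weeks), and dose (number of sessions attended", along with participant characteristics. Modality and duration are listed as two factors, each with its own two levels.

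**The concern.** The analysis section presents the separate effects of modality and duration as a matter of sample size. If every remote course lasts 8 weeks and every in-person course lasts 1 week, the obstacle is that the two factors are the same split of the participants, and recruiting more people leaves it in place.

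At stake is the labelling of a result. If both terms enter one model, software will typically drop one and attach the whole difference to the other. If they are tested in separate models, nothing is flagged and the same contrast is reported twice, once as a modality effect and once as a duration effect. Either report would claim something the described delivery cannot show.

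**Working it through.** The article gives no sample size, power or number enrolled for this analysis, so there is no planned figure to reproduce. The check is one of identifiability.

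**Inputs**
- Formats delivered: "remote, 8-week MBSR courses via Zoom and intensive week-long, in-person MBSR courses" (Mindfulness-Based Stress Reduction, interventions). That is two cells.
- Factors to be evaluated: modality, two levels; duration, two levels; dose; instructor (MBSR Analysis).
- Comparison group: "Matched controls are identified for each MBSR participant by randomly selecting nonenrolled individuals from the WellNurse participant pool" (MBSR Analysis). Controls have no modality and no duration.

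**Step 1: MBSR participants only.** Let M = 1 for in-person and D = 1 for 8-week. Under the two formats described, M = 1 − D for everyone, so corr(M, D) = −1. The model

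Y = b0 + b1·pre + bM·M + bD·D + b2·dose

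becomes, on substituting D = 1 − M,

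Y = (b0 + bD) + b1·pre + (bM − bD)·M + b2·dose.

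Only the difference bM − bD can be estimated. Adding any constant to both bM and bD and subtracting it from b0 leaves every fitted value unchanged.

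**Step 2: adding controls.** Let G = 1 for MBSR participants and 0 for controls. Then G = M + D for everyone, so the group column is the sum of the other two. The data identify two quantities (in-person 1-week against controls, remote 8-week against controls), while the model asks for three parameters.

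**Step 3: numerical check of rank.** Pre-scores and doses were simulated and formats split 50:50. These are assumptions, and the result does not depend on them.

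| n | MBSR only: rank of 5 columns | With controls: rank of 6 columns |
|---|---|---|
| 50 | 4 | 5 |
| 267 | 4 | 5 |
| 1,000 | 4 | 5 |
| 100,000 | 4 | 5 |

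(267 is the number recruited to the whole project, used only as an illustrative n; the number in MBSR is not given.) Dose adjustment does not restore the rank. A random effect for class or instructor would not either, because it changes the error structure and not the fixed-effect columns.

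**Step 4: one term at a time.** A model with M alone estimates bM − bD. A model with D alone estimates bD − bM. These are the same contrast with the sign reversed.

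**Step 5: what would break the pairing.** Suppose, as an assumption not in the documents, that a share s of MBSR participants fell in one further modality-duration cell and the rest split equally between the two described. The model with intercept, pre-score, M and D then has full rank (4 of 4), with |r| = (1 − s)/(1 + s) and variance inflation factor (VIF) = 1/(1 − r²) = (1 + s)²/(4s).

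| s | \|r\| | VIF |
|---|---|---|
| 2% | 0.96 | 1.0404/0.08 = 13.0 |
| 5% | 0.90 | 1.1025/0.20 = 5.5 |
| 10% | 0.82 | 1.21/0.40 = 3.0 |
| 20% | 0.67 | 1.44/0.80 = 1.8 |
| 33% | 0.50 | 1.778/1.333 = 1.3 |

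So separation depends on whether such a cell exists and how large it is.

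**The case against.** **The text is a tentative outlook and fixes no model.** It speaks of what may be tested and of potential impact, and it does not say that modality and duration enter together. This stands and lowers the severity. It does not remove the point, because testing the terms singly yields one contrast under two names (Step 4).

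**A third format may exist or appear.** The article also says "MBSR was offered as an elective course to count toward the students’ elective requirements for Nursing", without modality or duration, and that staff were trained to "develop a group of certified MBSR teachers to support long-term project sustainability". Recruitment runs through December 2024, and the quality-improvement framework allows interventions to be altered. None of this excludes another pairing, but none describes one. The opening statement that "MBSR is an 8-week experiential program including 2.5-hour weekly class sessions and a 1-day silent retreat" is a general account of the program and assigns no modality. The finding is therefore conditional on the delivery described.

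**Larger samples do help.** They help for instructor, dose and participant characteristics, which the same sentence covers. For modality against duration they do not help by themselves.

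**Stronger readings that the documents do not support.**
- A reader might infer that a choice of format for the curriculum would rest on an unidentifiable effect. The Discussion says only that interventions shown to be effective will be built into a course; no choice between MBSR formats is documented. A choice between the two described formats would in any case use the combined contrast, which is estimable.
- A reader might infer that session counts necessarily differ by format. The number of sessions in the week-long course is not given.
- A reader might infer that the differing pre-to-post interval (about 1 against 8 weeks) biases the results. The article has controls assessed at the same intervals as MBSR participants, which deals with this when each format is compared with its own controls.

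**Conclusion.** The point holds as a conditional one. With only the two formats described, modality and duration are perfectly confounded: one parameter is not estimable at any sample size, and only the combined difference between remote 8-week and in-person 1-week can be reported. The conclusion rests on one assumption, that no other modality-duration pairing is delivered. The article describes and plans none.

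It would be wrong to infer that the MBSR evaluation as a whole is compromised. The main comparison with matched controls does not use either factor and is unaffected. The analyses concerned are secondary and exploratory, so the severity is minor to moderate.

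**What to change.** In the MBSR Analysis section:

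1. Replace modality and duration with one two-level factor, format (remote 8-week, in-person 1-week).
2. Estimate it as a group-by-format interaction, each format compared with its own matched controls assessed at the same intervals, and state that the result is a combined difference in modality and duration.
3. Analyse dose within format.
4. State that modality and duration will be reported separately only if a course that breaks the pairing is actually delivered, and give the number of participants in each cell when doing so.

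Keep the pre- and post-course assessments as the main time points. The week-14 survey can serve only as a supplementary time point for the outcomes it collects, such as stress, burnout and resilience. The mindfulness questionnaire is described only before and after MBSR, and time since the end of the course could differ by format at week 14.

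The cost is a change of wording. What is given up is two separate claims that the described delivery cannot support; no estimable quantity is lost.

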### Physical Activity Analysis

Data logs generated from Fitbit devices will be collected from the Fitabase platform [36], a partner to Fitbit, and raw data will be preprocessed, including merging the data of all participants in the study and purging the data set from empty cells or invalid data. The privacy-respected data set, besides participants' ID and event date, involves information on 3 major categories—sleep, activity, and wearing time—with each category covering more information in their respective parameters for a duration of fall and spring academic semesters. The sleep category provides information ranging from sleep minutes in rapid eye movement, deep, light, and total asleep minutes to sleep efficiency. The activity category is reporting time and distances traveled in very active, moderately active, lightly active, and sedentary modes, alongside calories, basal metabolic rate, and approximated heart rate levels. Analysis of the data set is done using the Python language [37] and the Scikit-learn [38], Pandas [39], Numpy [40], Matplotlib [41], and Seaborn [42] packages by applying the multiple linear regression method and also generating a heatmap of the parameters.

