### Measures

#### Comprehensive Wellness Survey

After completing a web-based consent form, participants complete a comprehensive health behavior survey. This survey is distributed during week 4 and again during week 14 (the week before finals week) in the fall and spring semesters. Week 4 was selected based on the typical nursing student’s academic loads and stress. Examinations and competency testing begin each semester’s third to fourth week, accelerating stress during those periods. Participants complete the comprehensive health behavior survey during designated class or work time. Additional measures are collected before specific engagement in targeted study interventions. Participants’ answers are tracked through the project using unique ID codes. As listed below, several variables are assessed to capture the health of nursing students. The comprehensive measurement strategy aligns with Priority Area 2 from the National Academy of Sciences [8], which recommends the longitudinal use of valid and reliable measurements of burnout and factors that mitigate burnout to drive effective interventions and data-driven decision-making at the organizational level.

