## Results

### Overview

The project was funded on January 1, 2022. Data collection started in March 2022. A total of 267 participants have been recruited. Results will be published after each semester starting in December 2023.

The primary study variables will be analyzed 4 times per year to track population outcomes and changes. Regression analysis will be conducted to examine the relationship of students’ on-time progression, stress, resilience, and burnout with physical and emotional health variables and on-time progression. Subanalysis will be conducted for unique groups such as first and fourth year students, faculty and staff, and graduate students, as well as students from historically underrepresented populations such as first-generation college students and racial and ethnic minorities. Additionally, program retention, on-time graduation, and faculty and staff retention will be tracked over time. The cost of implementing MBSR, massage therapy, MasterChef, and fitness events will be tracked to determine cost per student. Additionally, feasibility will be measured using qualitative focus group interviews with students who complete specific interventions along with attrition rates for completing specific interventions such as MBSR and MasterChef.

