#### Fitness

Physical activity reduces stress and anxiety [67-70], and stress and anxiety are associated with increased burnout and decreased resilience among nurses [52]. A review of 37 studies on Fitbit-based interventions demonstrated the effectiveness of this wearable technology for physical fitness support; wearing a Fitbit significantly increased daily step counts and moderate to vigorous physical activity and significantly decreased weight [69]. Although students have access to healthy food and physical fitness environments, nursing programs do not systematically integrate support systems that promote physical well-being [12,71-74]. The aim of this study is to examine the effect of fitness interventions on nursing students’, faculty’s, and staff’s burnout, resilience, fitness, and well-being.

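### The Fitbit plan names ordinary multiple linear regression for repeated dated records, with no step for within-person correlation and no stated wear-time rule for the days it purges

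*Protocol article*

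**What the plan says.** All of the Fitbit plan is in the protocol article, Results, Physical Activity Analysis.

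- **Preparation:** the logs are processed by "merging the data of all participants in the study and purging the data set from empty cells or invalid data".
- **Structure:** the file holds the participants' "ID and event date, involves information on 3 major categories" (sleep, activity and wearing time), "for a duration of fall and spring academic semesters".
- **Analysis:** the data set is analysed in Python "by applying the multiple linear regression method and also generating a heatmap of the parameters". The packages named are Scikit-learn, Pandas, Numpy, Matplotlib and Seaborn.

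The section names no outcome, predictors, unit of analysis or criterion for a valid day. Methods for correlated data do appear elsewhere in the article: multilevel modelling as a later option under MBSR Analysis, and repeated-measures ANOVA under MasterChef Analysis.

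**The concern.** A file identified by person and date holds many records per person, and days from one person resemble each other. Ordinary multiple linear regression treats every row as independent. If the daily rows go straight into the regression, the analysis counts many days from one person as if they were many people. Standard errors are then too small for any predictor that differs between people, and chance associations look established.

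The second issue is which days remain. Empty or invalid data are removed under no stated criterion. Non-wear may well be related to how active, rested or stressed a person is, so the remaining days may not represent the semester. A model that uses sleep and activity together needs both on the same row, so a day with good activity data but no sleep data would drop out of it.

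The article says that interventions found effective will be built into the standard nursing curriculum (Discussion, Principal Findings), so overconfident findings could have consequences.

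**Working it through.** The article gives no sample size, standard error or power for the Fitbit analysis, so there is no figure of its own to reproduce. The check asks what happens if the rows are person-days.

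**Inputs**
- People: "A total of 267 participants have been recruited" (Results, Overview). This is an upper bound on wearers, because the device is optional and has its own consent (Fitabase Data Collection).
- Days per person, m: not stated. The survey is given "again during week 14 (the week before finals week"), so a semester runs to at least 14 × 7 = 98 days, and two semesters to about 196. Assumed range: 14 to 196.
- Intraclass correlation of the outcome, ICC_y: not stated, assumed 0.1 to 0.5.
- Intraclass correlation of the predictor, ICC_x: not stated. It is taken from 0 (varies only from day to day) to 1 (constant within a person).
- Two-sided 5% test: assumed. The only significance level in the article is under MasterChef Analysis.

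**Formulas** (pooled ordinary regression, equal correlation between any two days of a person)
- Design effect: DEFF = 1 + (m − 1) × ICC_x × ICC_y
- True SE / reported SE = √DEFF
- True type I error = 2 × [1 − Φ(1.96 / √DEFF)]

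**Results.** The simulated figures come from 500 runs per setting with 267 people.

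| m | ICC_x | ICC_y | DEFF | SE ratio | Type I error | Simulated type I error |
|---|---|---|---|---|---|---|
| 98 | 0 | 0.3 | 1.00 | 1.0 | 0.05 | 0.05 |
| 98 | 0.1 | 0.1 | 1 + 97 × 0.01 = 1.97 | 1.4 | 0.16 | 0.18 |
| 98 | 0.3 | 0.3 | 1 + 97 × 0.09 = 9.73 | 3.1 | 0.53 | 0.50 |
| 98 | 1 | 0.3 | 1 + 97 × 0.3 = 30.1 | 5.5 | 0.72 | 0.74 |
| 14 | 0.3 | 0.3 | 1 + 13 × 0.09 = 2.17 | 1.5 | 0.18 | not run |
| 196 | 0.5 | 0.5 | 1 + 195 × 0.25 = 49.75 | 7.1 | 0.78 | 0.79 |

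Over the whole assumed range the SE ratio runs from 1.0 to 9.9. The upper end is m = 196, ICC_x = 1, ICC_y = 0.5, where DEFF = 1 + 195 × 0.5 = 98.5.

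In rows: 267 × 98 = 26,166 person-days. For a person-constant predictor with ICC_y = 0.3 they carry the information of 26,166 / 30.1 ≈ 869 independent rows.

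**Check of a remedy.** In the same simulations, one mean per person brought the type I error back to between 0.04 and 0.06 in every setting tried.

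**Purging.** No arithmetic applies, because the article gives no wear rates. Sleep, activity and wearing time are separate categories in the file, but the purge is described once for the whole data set with no rule by category.

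**The case against.** The strongest reply is that this is a condensed article. A study design protocol is registered separately and is not shown, and model detail is often left to such a document. The section does not say that a regression row is a person-day, so averaging to one row per person is not excluded. It does not say that whole rows are deleted either; removal cell by cell or category by category would fit the wording. It promises no standard error, P value or confidence interval. Many of the listed variables change from day to day, and the inflation disappears for a predictor with no between-person component.

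Most of this stands, and it makes the point conditional. It does not remove it. The section is not silent on method: it describes a file of dated records and names a regression that assumes independence, whereas correlated-data methods are named for two other components. None of the packages listed is a mixed-model tool. Basal metabolic rate, heart rate and habitual activity or sleep plausibly differ between people, so a zero between-person component is unlikely to hold throughout.

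Three stronger readings are tempting but not supported.

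- A reader might infer that total sleep and its stages will be entered together and make the coefficients unidentifiable. The text ("sleep minutes in rapid eye movement, deep, light, and total asleep minutes to sleep efficiency") lists what the sleep category contains; it is not a list of regressors.
- A reader might infer that wearing time goes unused. The section never says so, and wearing time may be what defines invalid data.
- The Fitness section states "The aim of this study is to examine the effect of fitness interventions on nursing" students, faculty and staff in terms of burnout, resilience, fitness and well-being. A reader might infer that this aim goes unaddressed because the Fitbit file holds none of the survey scores. Survey answers are tracked by unique ID, attendance is recorded, activity is measured before and after training, and the Overview plans a general regression of stress, resilience and burnout on health variables.

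**Conclusion.** The point holds in conditional form. As written, the plan applies ordinary multiple linear regression to repeated dated records with nothing to handle within-person correlation. If rows are person-days, which is the natural reading but an inference, standard errors are understated for every predictor with a between-person component.

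At 98 days per person, a nominal 5% test would have a true error rate anywhere from 0.05 to about 0.7 across the 98-day settings tabulated above. The position in that range depends on the predictor and on correlations that the article does not give. It would be wrong to say that the standard errors simply are far too small: the days per person and both correlations are assumptions, 267 is a ceiling on wearers, and no test is promised.

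Selection of days through purging is a plausible risk that the document neither quantifies nor guards against.

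**What to change.** In Physical Activity Analysis:

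1. State the unit of analysis.
2. Replace the ordinary regression with a linear mixed model with a random intercept per participant. Participant-clustered standard errors or person-level means are acceptable alternatives.
3. Define a valid day from wearing time, separately for activity and for sleep, and keep each day in every analysis for which its category is valid.
4. Report the days excluded per person, with a sensitivity analysis on the valid-day rule.

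This needs no new data and no new comparison group. The cost is a few sentences of wording, modest programming with one further Python package for the mixed model, and wider confidence intervals.
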